### Secondary outcomes

#### Professional quality of life

The Professional Quality of Life Scale (ProQOL-5) is a 30-item scale to assess one’s perceived quality of life about working as a helper and includes both the positive and negative aspects of this work. It is a 5-point Likert self−reporting scale and consists of three subscales of professional QoL: compassion fatigue (CF), burnout (BO), and compassion satisfaction (CS). For each of the sub-scales, scores are categorized as Low (22 or less), Moderate (between 23 and 41), or High (42 or more). With a low professional QoL, health workers may manifest a loss of self−worth and diminished productivity, and staff turnover can be affected.

#### General self-efficacy

The General Self-Efficacy Scale is a 10-item psychometric scale designed to assess optimistic self-beliefs to cope with difficulties in life. The scale was developed to assess optimism referring to the personal belief that one’s actions are responsible for successful outcomes. The total score is 10 to 40. Higher scores indicate higher perceived general self-efficacy, and lower scores indicate lower perceived general self-efficacy.

#### Positive psychological change after the experience of traumatic events

PTGI (Post-traumatic Growth Scale) is used to demonstrate positive outcomes of the emergency events; for example, health care workers show improved psychological functioning in specific domains and a sense of increased job competency and confidence. The PTGI consists of 21 items, each rated on a 6-point-Likert scale (ranging from 0 = I did not experience this change due to my crisis to 5 = I experienced this change to a very great degree as a result of my crisis). In each of the five domains, changes may occur at the affective, cognitive, and behavioral levels. The mean PTG score reported of 55.94 was considered a moderate level of PTG. A similar mean score of 51.36 (SD = 19.90) was reported in Jordan and in Turkey (*M* = 49.11, SD = 29.11).

### Economic measures

#### Resource use

Key resource use and costs will be estimated based on the health provider perspective, which means the relevant costs including time spent by individuals on developing or delivering the trainings such as mental health professionals and training management (administrators, team members, psychiatrists, psychologists, and training assistants) and supervision. In addition, the time and costs associated with the training development, consumables/materials costs, travel cost, trainers’ wages and trainees’ time costs Cost and effect data are collected within a 12-month time horizon and were therefore not discounted.

#### Costs

Intervention costs will be estimated using bottom-up micro-costing and include labor costs of the program trainers, staff training costs, material costs, travel costs, and accommodation costs (17). Labor costs are based on the local average wage of hour per program meeting per program trainer (6 h in total for PFA and 4 h for control). Labor, training, managerial, and travel costs were based on an average time investment of per training session per session trainer. Training costs were based on full staff compliance with the program (16 h for clinical health care workers, 16 h for training management workers). Labor and training costs are valued using gross hourly wages. Costs will be expressed in 2021/2022 RMB yuan (¥). A detailed list of relevant resource use categories, sources of usage data, and unit costs are given in Table 3.

**TABLE 3 T3:** Resource use and intervention costs.

Cost item	Source	Unit cost	Calculation
**Pre-training costs**			
Curriculum design	Trial budget	¥ 500 per session	No of sessions *X* value of the course
Materials: participant manuals	Trial budget	¥ 50 per person	No of manuals = total number of participants (1260 + 79 + 60 = 1399)
**Train the trainer training venue**			
Instructor	Trial Expert Time Use Records	¥ 1000 per day	No of training days × value per day
Meals and tea break	Trial budget	¥ 50 per person	No of trainers × value per person
Trained trainer (Clinical psychologists)	Trial budget	¥ 60 per hour	Hours of work leave × daily wage
**Train the trainees training venue**			
Online Training Equipment	Trial budget	¥ 500 per day	No of days × price per time
Trained trainer (Clinical psychologists)	Trial budget	¥ 60 per hour	Hours of work leave × daily wage
Training assistant	Trial budget	¥ 200 per person-day	days of work × unit wage
Hardcopy of certificates for the trainees	Trial budget	¥ 50 per person	No of participants x (certificate cost + delivery fees)
**Indirect costs**			
Absenteeism	Ministry of Human Resources and Social Security of China “Enterprise salary survey information in 2020”	Attendee number and their daily wages according to profession classification assigned (Chinese National Ministry of Finance)	Days of work leave × daily wage

Healthcare costs will be estimated using tariffs from the Chinese Health Statistical Bureau.

Data on willingness to pay for the training program are collected by asking participants the question “Would you pay (about as RMB of 2022) to participate in the training program?”. The amount RMB was determined based on local cost information. Once the training materials are prepared, and the training contents are standardized, it may be possible to reduce the cost of the training program per participant to this level in the future. This hypothetical question is not accompanied by any actual payment for a training fee and does not penalize respondents who give an affirmative answer. The willingness-to-pay question is hypothetical also in that when the question is asked of the training participants during the follow-up surveys it will be whether they would pay to participate in the training program if they had not received the training.

However, this question may overestimate the importance of involvement in training. Blumenschein (18) performed laboratory tests to find a way to eliminate such bias in replies to hypothetical questions in general and concluded that the “certainty approach” can reduce the prejudice to a negligible degree. We use this strategy, which is the same as asking an additional question, “How confident are you about the response?” if the above willingness-to-pay question was positive, with dichotomous options of “absolutely sure” or “probably sure,” and only counting “certainly sure” as the affirmative answer.

### Analysis

#### Data analysis

Statistical analysis will be performed using STATA (version 17 or later) and a *p*-value < 0.05 (two-tailed) will be taken to indicate statistical significance.

All trial participants who were randomly assigned at the start of the trial will stay in the sample for analysis under the intention-to-treat principle. It will be decided whether the intervention program is effective using random effect mixed modeling described below. Demographic factors will be evaluated for their potential influence on primary and secondary outcomes, and in cases where they do, they will be used as covariates.

The primary outcome for the statistical analysis will be the mean change in PFA-SKA score after 2 months of follow-up compared between intervention and control arms. The analysis allowed for this clustering in order to obtain unbiased estimation of the treatment effect and its standard error (SE). A two-level hierarchical mixed-effects model will be used to be fitted in the statistical analysis plan.

All secondary outcomes will be summarized by trial allocation group and follow-up period using mean, SDs and 95% CIs for the variables (ProQOL, GSE, PTGI scores). Statistical tests of differences for secondary outcomes will be performed using the same hierarchical mixed-effects model as the primary outcome analysis. In addition, participant-scores are also compared as change from post-training to 2-month follow-up using independent group t-tests.

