**Method:**

This paper describes the protocol for a cluster randomized two-arm controlled trial. A total of 1,399 non-specialist health care workers will be recruited in 42 hospitals and health care centers across six provinces in China. Participants will be assigned according to hospital or health care center site to one of two groups (*n* = 699 for intervention group and 709 for control group) to receive system based PFA training or PFA training as usual. Both groups will receive one-day of training, comprising six modules including PFA core concepts, knowledge, skills and practice. Their knowledge, skills, competency, self-efficacy, resilience, and professional quality of life will be assessed immediately after the training; and reassessed after 1 and 2 months.

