### Hypothesis

Non-specialist health workers in the system based training arm will show superior improvement in the primary outcome in non-specialist health workers’ mental PFA proficiency. The intervention arm will also show favorable cost effectiveness.

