### Study procedure

Participants will receive face-to-face or online one-day training intervention including six sessions, with follow-up assessment at 1 and 2 months after training. Before the training, participants will be selected for study eligibility according to the study’s inclusion and exclusion criteria. They will be evaluated by a research staff blinded to the intervention in each hospital. After the selection, participants will be assigned to one of the two groups and informed by message about their training (place and time). Groups of participants will receive training according to their random assignment group. There will be three assessment points for the intervention and control groups: (1) immediately post training, (2) one month post training, and (3) two months post training. Assessments will be undertaken remotely, with online instruments. An overview of the protocol procedure is provided in Figure 1.

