#### Populations under investigation

Any participant with any post-baseline follow up will be included in the modified intention to treat (ITT) population. We will remove the missing data from analyses using listwise or pairwise deletion. A multilevel multivariable linear model does not substitute missing values; it uses all of the data for each participant that are available. The full data sets of participants who finish all sessions of the training and respond to the first round interview will be the basis for the protocol analysis.

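### The primary outcome is a change in PFA-SKA score, but the stated schedule has no pre-training score, and the only change over follow-up that it allows subtracts the effect already present after training

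*Protocol article*

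**What the plan says.** In the protocol article, the Data analysis section sets the primary outcome as "the mean change in PFA-SKA score after 2 months of follow-up compared between intervention and control arms". That sentence does not name the time from which change is measured. The same section adds independent-group t-tests in which scores are "compared as change from post-training to 2-month follow-up".

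The Hypothesis section says that the intervention arm "will show superior improvement in the primary outcome", and the Research question also speaks of change in proficiency.

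The schedule is given twice. Study procedure lists "1) immediately post training, (2) one month post training, and (3) two months post training". The Method part of the abstract says that outcomes "will be assessed immediately after the training; and reassessed after 1 and 2 months". The pre-training step in Study procedure concerns eligibility: "Before the training, participants will be selected for study eligibility according to the study’s inclusion and exclusion criteria".

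Populations under investigation refers to a baseline: "Any participant with any post-baseline follow up will be included in the modified intention to treat (ITT) population". Repeated measures modeling uses three times, T0, T1 and T2, and bases its data on the post-training interview and two follow-ups.

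The Sample size section plans for a difference between groups in mean competency score immediately after training and at both follow-ups.

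**The concern.** A change score estimates a training gain when its starting value was taken before the training. Here every scheduled score comes after it. The immediate post-training score is itself an outcome of the randomised training, so subtracting it removes the between-arm effect that exists at that moment. What remains compares how the arms move after training: loss in one arm against loss, or further gain, in the other.

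The stake is the headline result. A training that works and is retained would be expected to show no between-arm difference in such a change. One that works and partly fades would be expected to show a difference favouring control, even though the intervention arm is still ahead at 2 months.

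**Working it through.** **1. Which change can be computed.** Setting the sections side by side:

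| Section | What it requires or provides |
|---|---|
| Research question, Hypothesis | change or improvement in proficiency |
| Data analysis, primary outcome | mean change after 2 months, reference not named |
| Abstract (Method), Study procedure | three scores, all after training |
| Data analysis, t-tests | 2 months minus post-training |
| Populations under investigation | follow-up after an unscheduled baseline |
| Sample size | difference in mean score (a level) |

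On this schedule, the only change spanning the 2-month follow-up is 2 months minus immediate post-training.

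**2. Reproducing the planned sample size.** Inputs from the Sample size section: d = 0.43, ICC 0.2, power 0.80, alpha 0.05, 21 clusters per arm, 30 per cluster, 10% drop-out. Two-sided testing is from Data analysis.

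- Individually randomised: 2 × ((1.96 + 0.842)/0.43)² = 84.9 per arm.
- Design effect: 1 + (30 - 1) × 0.2 = 6.8.
- Per arm: 84.9 × 6.8 = 577.3, and 577.3/30 = 19.2 clusters, so 20 by the normal approximation. With a t-test on 2(k - 1) degrees of freedom, power is 79.5% at 20 clusters and 81.5% at 21.
- Total: 42 × 30 = 1260, and 1260/0.9 = 1400, against the stated 1399.

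At 21 × 30 per arm, the effective size is 630/6.8 = 92.6 and the noncentrality is 0.43 × √(92.6/2) = 2.93. Power on 40 df is 0.815. The plan's figure therefore reproduces, for a difference in *level*.

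**3. What the change contrast would show.** Let the between-arm effect be 0.43 SD immediately after training, and let a fraction r of it remain at 2 months. Then:

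difference in change = 0.43r - 0.43 = 0.43(r - 1)

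| r (assumed) | Between-arm level at 2 months (SD) | Difference in change (SD) |
|---|---|---|
| 1.25 | 0.54 | +0.11 |
| 1 | 0.43 | 0 |
| 0.75 | 0.32 | -0.11 |
| 0.5 | 0.215 | -0.215 |

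At r = 1 the change test rejects 5% of the time, while the level test at 2 months has 81.5% power.

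**4. How often the misleading direction would reach significance.** At r = 0.5, take the SD of change as √(2(1 - ρ)), where ρ is the within-person correlation, and the standard error as SD × √(2(1 + 29 × ICC)/630). The documents give neither ρ nor the ICC of change, so both are assumed. With ρ = 0.5 and ICC 0.2, the test is significant about 30% of the time. With ρ = 0.8 and ICC 0.05, the figure is about 96%.

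**The case against.** **The reference for change is inferred.** The primary-outcome sentence names none. The explicit post-training-to-2-month wording belongs to a supplementary t-test at the end of the secondary-outcomes paragraph. This stands: the article does not say outright that the primary change starts at the post-training score. It does not rescue the endpoint, though. Either the reference is the one the schedule allows, or the schedule contains none.

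**A pre-training score may exist but be unlisted.** The baseline wording in Populations under investigation and the blinded evaluation mentioned around selection could hint at one. T0 is not explicitly defined, Figure 1 is not shown, and an article condenses the full protocol. The hint is weak, because Study procedure counts exactly three points and the abstract agrees. If a pre-training score is taken, the sections still contradict each other.

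**Stronger readings that a reader might infer:**

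- *The trial cannot show a training effect.* Not supported. Hospitals are randomised, so a between-arm comparison of levels after training estimates the effect without any baseline. The Sample size section plans for that comparison, and the mixed model includes treatment condition as a factor.
- *The repeated-measures test is faulty in the same way.* A group-by-time test would be, but the article does not name one as the efficacy test.
- *The cost-effectiveness ratio subtracts the post-training score.* Neither the abstract nor the Within-trial cost-effectiveness analysis section says so. Both can be read as a between-arm difference at 2 months.
- *The endpoint measures decay.* Too narrow, since skills could also consolidate after training and give a positive contrast.

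**Conclusion.** The point holds as a fault in how the primary endpoint is defined: wrong as written, and in need of correction before analysis. The stated change has no pre-training reference in the stated schedule. Read in the only way the schedule permits, it removes the effect already present after training. It also differs from the quantity for which the trial was sized.

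Given the planning effect immediately after training, the expected change contrast is 0 with full retention and -0.215 SD with half retained, against 81.5% power for a 0.43 SD level difference. The sign and size depend on the assumed retention. The conflict between endpoint, schedule and sample size does not.

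**What to change.** 1. Define the primary endpoint as the between-arm difference in SKA-CPFA score at 2 months. Estimate it as the arm contrast at that time from the clustered mixed model. The immediate post-training score may remain as one of the repeated responses, but it must not be subtracted, used as a covariate or constrained to be equal between arms.
2. Do not use the post-training-to-2-month t-test as an efficacy test.
3. State that the within-trial cost-effectiveness analysis uses the same 2-month between-arm difference.
4. Reconcile Research question, Hypothesis, Study procedure, Data analysis, Repeated measures modeling and Populations under investigation. Define T0, and replace the baseline wording if no baseline is taken.

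These steps cost only wording, need no new data and leave the sample size unchanged.

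Optionally, if training has not started, collect one online SKA-CPFA score before training and before allocation is disclosed, and use it as a covariate. The cost is a short extra questionnaire and possible pre-test sensitisation. That may differ between arms, because the instrument covers PFA content while the control training is based on mhGAP.

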### Sample size

The total sample size of 1399 health care workers was estimated with a power = 0.80 and an alpha = 0.05, using PASS software based on *d* = 0.43 (12) and an ICC of 0.2 estimated in a similar study conducted in Nepal (13). The total minimum required sample size was 21 clusters per arm with 30 participants with an additional 10% inflation for drop out in each cluster to show a 20% difference in mean competency score on the psychological skills and knowledge (14) between the intervention group and control group immediately after training and at 1 and 2 month the follow-ups.

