#### Repeated measures modeling

For the primary and secondary outcomes, repeated measures will be used in a linear mixed model. ANOVA with time (T0-T1-T2) as a within-groups component and treatment condition as a between-groups factor will be utilized. Mixed-model repeated measures ANOVA does not substitute missing values; it uses all the data for each participant that are available. We’ll run a sensitivity analysis to examine the effect of drop-outs on our findings. The full data sets of participants who finish all sessions of the training will be the basis for the protocol analysis. The time to onset of clinical outcomes will be based on post-training interview and two follow-up assessments. The pooled standard deviations will be used to calculate the effect sizes (Cohen’s d) within and between groups. Appropriate statistical tests will be used to explore differences between intervention and control groups (Fisher’s exact test as appropriate). The nature of the routine administrative data will determine the test’s selection. SPSS statistics, Excel, and Visual Basic for Applications will be used for all analyses (VBA).

The multilevel analysis will be used with nested data to account for clustering and adjust for the type of critical incident, age, and sex. Means and standard deviations for continuous outcomes and proportions for categorical outcomes will be reported.

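### The added t-tests on participant change scores ignore the randomised hospitals, contradicting the plan's own statement that the analysis allows for clustering; their true error at a nominal 5% depends on a change-score ICC that is not given

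*Protocol article*

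**What the plan says.** All references are to the protocol article.

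- **Unit of randomisation.** Setting and participants, and Randomization and allocation concealment, allocate whole hospitals, 21 to each arm. Staff follow their hospital.
- **Design assumptions.** Sample size uses "an ICC of 0.2 estimated in a similar study conducted in Nepal" and "21 clusters per arm with 30 participants with an additional 10% inflation for drop out in each cluster".
- **Main analysis.** Data analysis says that effectiveness will be decided by mixed modelling and that the primary analysis allows for clustering so that the effect and its standard error are estimated properly: "A two-level hierarchical mixed-effects model will be used to be fitted in the statistical analysis plan". The primary outcome is a mean change in score at 2 months. Secondary outcomes use the same model.
- **Added test.** The paragraph on secondary outcomes ends with a further comparison: "participant-scores are also compared as change from post-training to 2-month follow-up using independent group t-tests". No adjustment for hospital is mentioned. The section's general rule for significance is p "< 0.05 (two-tailed) will be taken to indicate statistical significance".
- **Repeated measures.** Repeated measures modeling places the scores in a linear mixed model and adds: "ANOVA with time (T0-T1-T2) as a within-groups component and treatment condition as a between-groups factor will be utilized". It allows Fisher's exact test where appropriate for exploring differences between arms, and it closes by saying that a multilevel analysis will account for clustering.

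**The concern.** An independent-group t-test takes its standard error from the spread between individuals. When hospitals are randomised, any hospital-level variation in the tested score also moves the arm means. The t-test does not count that variation at its full weight, so its standard error is too small whenever the tested score is correlated within hospitals. A plan that says it allows for clustering and then adds such a test contradicts itself.

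The results would carry two p-values for much the same question, and the invalid one would tend to be the smaller. The added test may also reach the primary measure. Study procedure lists three assessments, all after training, so a change ending at 2 months appears to start at or after the post-training visit. The sentence stands in the paragraph on secondary outcomes, but its wording does not restrict it to them.

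The ANOVA and Fisher's test raise a related but weaker question, because the plan names no hospital term for either.

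**Working it through.** **Inputs from the plan.** Two-sided alpha 0.05 and power 0.80; effect size and correlation from "0.43 (12) and an ICC of 0.2"; 21 hospitals per arm; m = 30 analysed per hospital (about 33 recruited).

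**Step 1: reproduce the plan's own figure.**
- Per arm without clustering: 2 × ((1.960 + 0.842)/0.43)² = 84.9, so 85.
- Design effect: DE = 1 + (m − 1) × ICC = 1 + 29 × 0.2 = 6.8.
- Per arm with clustering: 84.9 × 6.8 = 577, and 577/30 = 19.2, so 20 hospitals by the normal approximation.
- With a noncentral t on 2k − 2 degrees of freedom, power is 79.5% at k = 20 and 81.5% at k = 21. The stated 21 is the minimum.
- 42 × 30 = 1,260, and 1,260/0.9 = 1,400, against the stated 1,399.

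The design therefore rests on clustering, with a design effect of 6.8 at ICC 0.2.

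**Step 2: error rate of a test that ignores hospital.** If the tested variable has within-hospital correlation ICC, the test statistic under the null has variance of about DE instead of 1. The true two-sided error is 2 × (1 − Φ(1.96/√DE)).

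| ICC of the tested score | DE (m = 30) | 1.96/√DE | True error, m = 30 | True error, m = 33 |
|---|---|---|---|---|
| 0 | 1.00 | 1.96 | 5.0% | 5.0% |
| 0.01 | 1.29 | 1.73 | 8.4% | 8.8% |
| 0.02 | 1.58 | 1.56 | 11.9% | 12.6% |
| 0.05 | 2.45 | 1.25 | 21.1% | 22.4% |
| 0.10 | 3.90 | 0.99 | 32.1% | 33.9% |
| 0.20 | 6.80 | 0.75 | 45.2% | 47.1% |

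**Step 3: which row applies.** The t-test is on change. A hospital effect that is the same at both visits cancels in the difference; only hospital variation specific to a visit remains. The ICC of change is therefore (hospital-by-visit variance)/(hospital-by-visit variance + residual variance), and it need not equal the ICC of a single score.

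A simulation under the null checked this: 42 hospitals of 30, three visits, 3,000 runs, single-score ICC held at 0.2. The participant and residual variances of 0.4 each are assumptions, not figures from the plan.

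| Hospital variance specific to a visit | ICC of change | t-test on change rejects | t-test on hospital means rejects |
|---|---|---|---|
| none of 0.20 | 0 | 4.9% | 4.8% |
| 0.02 of 0.20 | 0.02/0.42 = 0.048 | 20.5% | 4.9% |
| 0.10 of 0.20 | 0.10/0.50 = 0.20 | 45.3% | 5.1% |

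The simulated rates agree with the formula. The test on hospital means holds its 5% throughout.

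**Step 4: ANOVA and Fisher's test, only if fitted without hospital.** In the same simulations an ANOVA with no hospital term rejected 48% to 52% of the time for the arm main effect and 5% to 65% for arm by time. Fisher's test on a score split at its mean (1,000 runs) rejected 35% to 37%. These figures show why the wording needs settling. They do not show that the plan will fit the tests this way.

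**The case against.** The strongest reply is that the plan already names its basis for judging effectiveness. That basis is a mixed model allowing for clustering, with secondary outcomes analysed the same way. The t-tests come afterwards as an extra. This stands, and it limits the harm to supplementary p-values. It does not make those p-values valid.

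A reader might infer four stronger things, none of which the article supports:

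- **That the t-tests reject 45% of the time.** This needs an ICC of 0.2 in the change score. Sample size does not say which score its 0.2 refers to. If hospital effects are fully stable over time, the error is the nominal 5%.
- **That the ANOVA is unclustered.** It is described within text on a linear mixed model, the section ends with a multilevel analysis to account for clustering, and the abstract speaks of a multi-level model for the repeated measures. Naming time and arm as factors does not exclude a random hospital effect. The text is ambiguous.
- **That Fisher's test will be used on trial outcomes.** It is offered for exploration, as appropriate, with the choice of test depending on administrative data. No named outcome is assigned to it.
- **That the two-level model lacks a level.** Participants within hospitals are the right two levels for one change score per person, which is how the primary outcome is defined. A gap arises only if three scores per person enter a two-level model with no within-person covariance. Repeated measures modeling states no number of levels.

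**Conclusion.** The point holds for the independent-group t-tests. They are stated without allowance for the randomised hospitals and contradict the plan's own account of its analysis. Their true error at a nominal 5% is about 5% if the change-score ICC is 0, 12% at 0.02, 21% at 0.05, 32% at 0.10 and 45% at 0.20, assuming equal hospitals of 30. The ICC of change is not given. The value 0.20 is the highest examined, not a proven ceiling. An error of exactly 5% needs no hospital-by-visit variation at all, which is hard to presume when training is given to groups, face to face or online, with a facilitator at each site.

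The consequence is invalid supplementary p-values that could sit beside, and disagree with, the mixed model. The decision on effectiveness does not rest on them. For the ANOVA, Fisher's test and the number of levels, the finding is that Data analysis and Repeated measures modeling need reconciling, not that either specifies a wrong model.

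**What to change.** 1. Delete the independent-group t-tests. If a separate comparison of the change from post-training to 2 months is wanted, take it from the hierarchical model, or use a t-test on the 42 hospital mean changes (40 degrees of freedom).
2. In Repeated measures modeling, state that the ANOVA or mixed model includes a random hospital effect and, where three scores per participant enter, also within-participant correlation (a participant effect or a within-person covariance). Make this agree with the two-level model in Data analysis.
3. For any between-arm comparison of an outcome, use a cluster-adjusted method in place of Fisher's exact test.
4. Keep the primary contrast as the mean change that Data analysis defines, so that the correction does not alter the quantity estimated.

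This changes analysis wording only and needs no new data or participants. The downside is that some supplementary p-values become larger.
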